## Abstract

**Background:**

We recently completed a randomized clinical trial of two minimally invasive surgical procedures for stress urinary incontinence, the retropubic tension-free vaginal tape (TVT) versus the trans-obturator tape (TOT) procedure. At one year postoperatively, we were concerned to find that a significant number of women had tape that was palpable when a vaginal examination was undertaken. Because the risk factors for adverse outcomes of tape surgery are not clearly understood, we are unable to say whether palpable tapes will lead to vaginal erosions or whether they merge into vaginal tissue. We do not know whether patients go on to have further adverse consequences of surgery, leading to additional cost to patients and healthcare system. Our current study is a 5 year follow-up of the women who took part in our original trial.

**Methods/Design:**

All 199 women who participated in our original trial will be contacted and invited to take part in the follow-up study. Consenting women will attend a clinic visit where they will have a physical examination to identify vaginal erosion or other serious adverse outcomes of surgery, undertake a standardized pad test for urinary incontinence, and complete several health-related quality of life questionnaires (15D, UDI-6, IIQ-7). Analyses will compare the outcomes for women in the TOT versus TVT groups. The cost-effectiveness of TOT versus TVT over the 5 years after surgery, will be assessed with the use of disease-specific health service administrative data and an objective health outcome measure. A cost-utility analysis may also be undertaken, based on economic modeling, data from the clinical trial and inputs obtained from published literature.

**Discussion:**

This study is needed now, because TOT and TVT are among the most frequently conducted surgical procedures for stress urinary incontinence in Canada. Because stress urinary incontinence is so common, the impact of selecting an approach that causes more adverse events, or is less effective, will have a significant impact on individual quality of life, and societal and health care costs.

**Trial registration:**

ClinicalTrials.gov NCT00234754. Registered October 2005.

## Background

A 2010 Health Canada notice described "*Complications Associated with Transvaginal Implantation of Surgical Mesh for the Treatment of Stress Urinary Incontinence and Pelvic Organ Prolapse*" [1]. The warning highlighted longer term complications associated with the use of transvaginally-placed mesh for the treatment of stress urinary incontinence (SUI), including erosion of the tape through the vaginal epithelium, pain including dyspareunia, and infection. The notice also stated that risk factors associated with these complications are not completely understood. Health Canada therefore advised surgeons to seek specialist training in the use of mesh devices, to discuss possible adverse events with patients before surgery, and to warn patients that additional surgery may be required to address complications. They also noted that such surgery may not fully correct any adverse effects. A similar memo was circulated by the FDA in 2008, stating that over 1000 adverse events had been reported [2].

New devices are being introduced frequently for SUI, because it is a common condition [3-5] which is becoming more prevalent as a result of our aging population [4-6]. In addition, many patients are less tolerant of symptoms, embarrassment and inconvenience caused by SUI [6].

There has been increasing concern about the introduction of new surgical devices into urogynaecology without evidence of safety and effectiveness[7-9]. Device manufacturers are not required to provide such information to obtain a license in Canada, the USA or Europe, if a device is made by a manufacturer who makes similar products or if a similar product is already produced by another manufacturer [10-12]. Therefore it becomes the responsibility of clinicians to evaluate any known relevant evidence [7-9,13]. Unfortunately even if short-term outcome is known, longer term outcomes usually remain unknown, and therefore clinicians are unable to fully inform patients of the consequences of surgery.

Clinical trials in surgery are difficult to do, particularly when new devices are widely adopted early [13]. There is no incentive for device manufacturers to provide long-term evidence of safety and effectiveness, and it is difficult for independent researchers to obtain funding, because there is a perception that licensed devices must be safe. In addition, it is difficult to recruit patients to device trials [14,15]. Thus there is a scarcity of longer term evidence.

We recently completed a randomized clinical trial of two stress incontinence procedures, finding concerning clinical outcomes at one year, with a significant number of women having tape that was palpable when a vaginal examination was undertaken at one year [16]. Because the risk factors for adverse outcomes of tape surgery are not clearly understood [1,2], we are unable to say whether palpable tapes will lead to vaginal erosions or whether they merge into vaginal tissue. We do not know whether patients go on to have further adverse consequences of surgery, leading to additional cost to patients and healthcare system.

### The problem to be addressed

#### Stress urinary incontinence (SUI)

Urinary incontinence (UI) is a prevalent condition that affects approximately 27% of women worldwide [3,5] with far-reaching physical, psychological, social, and economic implications. Incontinence has been found to reduce health-related quality of life to roughly the same degree as chronic conditions such as depression and Type I diabetes [17]. Personal consequences include restriction of physical and social activity, self-imposed social isolation [18,19], and sexual dysfunction [20]. UI is also a major factor contributing to nursing home admission and hospital readmission among older women with co-morbid conditions [21,22]. With direct costs estimated at over 25 billion dollars per year in the United States (approximately 3,500 dollars for each incontinent person) [23,24] and 1.5 billion dollars per year in Canada [25], UI is associated with major individual, societal, and health care costs.

SUI is the most common form of UI in women 60 years of age or younger and is a contributing factor for the majority of older women with incontinence [26,27]. Women with SUI experience leakage associated with increases in intra-abdominal pressure, such as with physical exertion, coughing, laughing, and/or sneezing. Physiological factors include anatomical defects in pelvic support structures and/or neuromuscular dysfunction affecting urethral pressure [28]. Women with a family history of SUI are twice as likely to have SUI compared to those without a family history [5]. A predisposition gene for pelvic floor disorders including SUI was recently described [29]. First line treatment is usually conservative, for example for example pelvic floor muscle exercises [30]. In cases where conservative therapies fail, women may opt for surgical treatment [31]. Surgical treatments for SUI are among the most common of all female surgeries [32].

#### Tape surgeries for SUI

Since it was introduced in 1996, the minimally invasive retropubic tension-free vaginal tape (TVT) [33-41] has become the surgery of choice for treating stress urinary incontinence. Concern about complications associated with TVT [37-41] led in 2001 to the development of another minimally invasive procedure using the trans-obturator tape (TOT) procedure [42].

Prior to introducing TOT into clinical practice in Calgary, we conducted a trial of 52 TOT procedures, using the Obtape device. At 12 months postoperatively, the vaginal erosion rate was found to be unacceptably high (15%) [43]. We believed that the high rate of erosions was associated with the specific polypropylene mesh (pore size 50 μm) used in the Obtape device [44], but we remained concerned that the trans-obturator approach itself could be at fault. We decided to undertake a randomized trial comparing TOT to TVT using surgical devices from a single manufacturer, that incorporated a type of polypropylene mesh which was completely macroporous (pore size >75 μm), to permit infiltration by macrophages, fibroblasts and blood vessels [44]. Our trial was designed to compare the effectiveness of the surgical approach of TOT to TVT in terms of objective cure of stress urinary incontinence (SUI) at 12 months postoperatively (NCT002237540) [16]. We also conducted a health economic evaluation alongside the RCT [45].

In our RCT, women with SUI were randomly allocated to either TOT or TVT procedures, and reviewed at 12 months after surgery. Primary outcome was objective evidence of "cure" evaluated by standardized pad test ("cure" defined as <1 g urine leaked). Other outcomes included: complications; subjective cure; incontinence-related quality of life; return to usual sexual activity; and satisfaction with surgery. Primary analysis compared the proportion of patients in each group who were cured at 12-month follow-up.

One hundred and ninety-nine women were randomized (94 in the TOT, 105 in the TVT group). 68 women (81%) in the TOT group were cured, versus 67 (77%) in the TVT group (RR 1.05, 95%CI 0.90 to 1.23, p = 0.58). On vaginal exam, the tape was palpable for 68 women (80%) in the TOT and 24 (27%) in the TVT group (RR 0.22, 95%CI 0.13 to 0.37, p < 0.001), and more women in the TOT group experienced groin pain during vaginal palpation (13 (15%) versus 5 (6%) in the TVT group, p = 0.04). Quality of life improved significantly from baseline in both groups (30 point improvement in IIQ-7 score, both groups).

At 12 months, the majority of women had minimal leakage, and their quality of life had improved significantly, but differences were not observed between groups. The presence of palpable tape, particularly among the TOT group, was concerning: longer follow-up is needed to estimate if this outcome leads to vaginal erosion or resolves over time. We concluded that until long-term follow-up is available, TVT should remain the mid-urethral sling procedure of choice [16].

Our economic evaluation was a cost utility analysis, using data collected in the trial, as well as administrative utilization and cost data [45]. The findings from the cost utility analysis suggest that TOT is a cost-effective alternative to TVT in the treatment of SUI, perhaps as a result of underlying difference in utilization of various health services following randomization [45].

#### Synthesis

The clinical results from our RCT raise the possibility that the TOT approach may lead to more women having longer term problems if those with tapes found to be palpable at 12 months go on to develop vaginal erosion. However our economic evaluation suggested that TOT may be more cost effective than TVT. The apparently contradictory results from our RCT and economic evaluation must be further investigated, to determine whether the TOT approach is safe and effective.

### Principal research questions

#### Primary question: safety

What is the incidence of vaginal erosion or other serious adverse outcomes of surgery among women who had a surgical procedure for stress urinary incontinence utilizing a TOT device, versus a TVT device, over the 5 years following surgery?

#### Secondary question: effectiveness

What are the objective and subjective outcomes of TOT compared with TVT at 5 years following surgery for SUI?

#### Secondary questions: health economics

What are the disease-specific rates of health service utilization related to repeat surgical intervention, as well as surgery and other treatment related to adverse events for women who had a TOT procedure, versus those who had a TVT procedure, over the 5 years after surgery?

Using economic modeling and cost utility analysis, is TOT cost-effective compared with TVT over the 5 years after surgery?

#### Other question

Do women with tape found to be palpable in the vagina at 12 months postoperatively, go on to develop vaginal erosion by 5 years following surgery?

### Literature review

Unfortunately there is very little evidence from clinical trials related to follow-up of patients for longer than a year after TOT versus TVT surgery.

#### Safety

A recent Cochrane review found that minimally invasive suburethral sling procedures (such as TOT and TVT) used for the surgical management of SUI produced more bladder perforations (TVT), but fewer other operative or short-term postoperative complications than traditional surgical procedures (such as slings, retropubic colposuspension and laparoscopic colposuspension) [46]. The review stated that minimally invasive suburethral sling procedures are the management of choice for SUI.

Three published systematic reviews with meta analyses compared complications rates associated with TOT versus TVT [47-49]. The reviews overlapped, presenting information on short-term outcome: Sung's study included six RCTs [47], Novara's included 14 [48], and Latthe's included 11 [49]. The TOT procedure produced fewer bladder perforations and hematomas, but more patients had groin pain at two months postoperatively. The meta analyses did not demonstrate significant differences in erosion rates or overactive bladder. Few of the included trials reported longer term follow-up (over 12 months), and the outcomes evaluated varied widely. In addition, most of the studies were described as being of limited methodological and clinical quality, and therefore the authors recommended that high-quality studies with longer term follow-up were needed [47-49]. A further review of literature published between January 2008 and January 2009 (including six RCTs) came to similar conclusions [50].

Despite the large number of trials of TOT versus TVT, the lack of long-term follow-up prevents surgeons and patients from being able to make treatment decisions on the basis of evidence of safety.

#### Effectiveness

The recent Cochrane review found that minimally invasive suburethral sling procedures (such as TOT and TVT) are as effective as traditional surgical procedures in the short-term [46]. Sung, Novara, Latte and Long examined the evidence of short-term effectiveness of TOT versus TVT, concluding that despite the large volume of research, there is no clear evidence to suggest that one of the two procedures is preferable to the other [47,49-51]. The maximum previously reported follow-up was 36 months [51]. The four reviews concluded that longer term follow-up is needed before a recommendation can be made regarding effectiveness.

#### Health economics

Despite the acknowledged cost of incontinence and concern about the economic burden of disease [23-25], few studies have examined the economics of surgical procedures for stress urinary incontinence. Papers have examined the costs of TOT versus Burch colposuspension [52,53], and TOT versus other surgical procedures [54]. TOT was found to be more cost-effective than other surgical procedures using RCT data up to 6 months [52], and using economic modeling up to 5 years [54] and 10 years [53].

A single study, using retrospective chart data and a Markov modeling, evaluated the cost of TOT undertaken as an inpatient procedure versus TVT as day surgery procedure, finding the day surgery more cost effective than inpatient surgery [55], but not commenting on the cost effectiveness of TOT versus TVT.

Our own economic evaluation using the data following women to 12 months in our TOT-TVT trial [45], suggested that TOT is a cost effective alternative to TVT in the treatment of SUI. However, these results must be confirmed using longer term follow-up.

#### Summary

The evidence from published studies provides evidence of safety and effectiveness in favour of TVT as a surgical treatment for SUI compared to more traditional approaches. Unfortunately there is insufficient evidence to compare the long-term outcome of TOT versus TVT as a treatment for SUI. Similarly, insufficient economic evidence is available to evaluate cost effectiveness or cost utility of TOT versus TVT. Our proposed study will address these issues.

## Methods/Design

### Trial design

The research is an extension to a trial previously conducted [16]. The new study further evaluates the safety, effectiveness and cost utility of the two devices, TOT and TVT. The study involves follow up of all participants from the initial trial, and includes physical examination and quality of life measurement. In addition, a health economic study is being undertaken. Ethics approval was provided by the University of Calgary Conjoint Health Research Ethics Board, Ethics ID 18421.

### Trial centres

Patients were initially recruited from three Calgary centres, with all follow-up carried out at the Calgary Pelvic Floor Disorders Clinic. All 5 year follow-up visits will similarly be conducted in the Pelvic Floor Disorders Clinic.

### Inclusion/exclusion criteria

All women included in the initial trial will be eligible for inclusion in the 5 year follow-up study.

#### Inclusion criteria

Women were included if they:

• had type II stress incontinence, defined as leaking with increased abdominal pressure [56,57].

• were eligible for both types of surgery.

#### Exclusion criteria

Women were excluded if at the time of the index surgery they:

• had vaginal prolapse requiring surgical repair at the same time as the index surgery

• had previously had incontinence surgery

• had overactive bladder or incontinence caused only by bladder overflow

• intended to have further children

• had Alzheimer's or Parkinson's disease, progressive neurological disease such as multiple sclerosis, or were immunocompromised

• were unable to understand English.

### Trial interventions

Women in the trial received the following interventions [16]:

#### Surgical care

All seven surgeons who participated in the trial were trained to undertake both the TOT and TVT procedures, and had carried out a minimum of 5 of each procedure as lead surgeon after training. At the time of the initial study, the TVT procedure was the surgical standard of care for stress incontinence in Calgary, and remains so to date.

Women in both groups had their surgery performed according to the usual practice of the operating surgeon. Anaesthesia was either general or local, depending on the clinical state and choice of the patient, and according to the usual clinical practice of the anaesthesiologist. Where possible, the operations were planned as day procedures.

#### TOT Group

The TOT procedure was carried out according to the device manufacturer's recommendations.

#### TVT Group

The TVT procedure was carried out according to the device manufacturer's recommendations.

#### Post-operative care for all patients

As usual in Calgary for day case patients, trial participants in the trial were cared for in their homes, unless a hospital stay was required for clinical or administrative reasons.

### Practical arrangements for allocating participants to trial groups

Consenting patients were randomly allocated to receive either a TOT procedure or a TVT procedure. The randomization list was generated by the study statistician (using ralloc procedure in Stata (StataCorp LP, Texas, USA)) using permuted block randomization with block sizes varying from 2 to 8, and stratified by surgeon. Randomization was carried out a few days before surgery, to ensure that the appropriate surgical device was available in the operating room.

### Methods for protecting against sources of bias

The initial trial was undertaken as a pragmatic trial [58]. Neither surgical team nor patient knew the next treatment allocation. Outcome measurement was not carried out blindly, but was conducted by a research nurse who was independent of clinical care. The vaginal examinations to palpate for tape erosion and pain were carried out by a clinician (MR) who had recruited 24 of the study patients. Although not informed of the patient's group of allocation at the time of vaginal examination, it became apparent that palpable tapes tended to be associated with TOT, and it was therefore not possible to maintain examiner blinding.

In the 5 year follow-up, similar considerations will apply. The research nurse who carried out the 12 month contacts and follow-up visits, and is therefore already known to study patients, will contact and follow all women at 5 years. The research nurse remains independent of clinical care. For the 5 year follow-up, all clinical examinations will be carried out by a urogynaecology clinical fellow who will be blinded to both group of allocation, and the presence of palpable tape at 12 months.

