#### Primary outcome: incidence of vaginal erosion or other serious adverse outcome

• **Incidence of vaginal erosion **will be determined by chart review and by standardised digital vaginal exam by a blinded examiner at the time of follow-up. The blinded examiner, a urogynaecology fellow, will be trained to undertake the standardized vaginal exam by MR. Any women who had additional treatment for vaginal erosion (any surgical treatment, or conservative treatment with vaginal estrogen), or who is found to have an erosion on digital exam, will be considered to have had a vaginal erosion.

• **Other serious adverse outcomes **will be defined as those occurring during the 5 years following index surgery which are considered to have a suspected "reasonable causal relationship" [59] with the TOT or TVT procedure. The adverse outcome will have resulted in further inpatient or outpatient treatment, an additional surgical or medical intervention, and/or cause persistent disability or incapacity. Possible adverse outcomes will include persistent groin pain and re-operation for SUI.

Women will be asked to recall any problems they believe they experienced as a result of surgery, and hospital charts will be reviewed for any possible adverse outcomes or complications. Details of additional treatment will be sought from the treating physician if treatment was provided elsewhere.

• **An independent adjudication committee **will be established to adjudicate all instances of a primary outcome (vaginal erosion or other serious adverse outcome). The adjudication committee will consist of three urogynaecologists not involved in the trial, from other institutions than the University of Calgary. They will be provided with all clinical details of the adverse outcome, with the cases blinded to group of allocation. The committee will be asked to judge whether each outcome can be defined as a serious adverse outcome and whether it has a "reasonable causal relationship" with the index surgery. Only if the adjudication committee agrees on both counts, will the adverse outcome be considered a primary outcome.

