#### Secondary outcomes

##### Objective outcome of SUI surgery at 5 years after index surgery, measured by pad test

Objective evidence of SUI at 5 years following surgery will be obtained using a standardised pad test (as used in our 12 month follow-up [16]), as follows.

• Retrograde filling of bladder with 300 ml sterile water

• Pre-weighed collecting device (pad) is put on and the test period begins

• During a 15 minute period the subject performs the following activities: walk up and down 1 flight of stairs; standing up from sitting, 10 times; coughing vigorously, 10 times; running on the spot for 1 min; bending to pick up small object from floor, 5 times; washing hands in running water for 1 min

• At the end of the test the collecting device is removed and weighed

• If test is representative, subject undertakes uroflow evaluation (check for voiding dysfunction)

Women will be considered "cured" if the pad weight gain is less than 1 g over the test period. This definition of cure was used in our earlier follow-up [16], allowing comparison with that study. This definition has also been used in other incontinence RCTs [34,60].

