### Recruitment rate

All women will be contacted initially by mail by the research nurse who did all the patient contact and follow-up evaluations at 12 months. Following the initial mail contact, which will include a description of the study and a consent form, women will be contacted by telephone to schedule a clinic visit. Women will be contacted for the new study two months before their 5 year anniversary, so that follow-up appointments can be scheduled to coincide as closely as possible with the anniversary of patients' index surgeries. Initial surgeries took place over a 21 month period, and therefore the 5 year follow-up visits will take place over a 21 month period, from October 2010 to June 2012.

We believe that we shall achieve good follow-up rates for this study. At 12 months follow-up, 182/199 (91%) study patients participated. We additionally sought consent from women to contact them again at 5 years postoperatively. We obtained consent from 171/199 patients (86%), with no responses from 28 patients (16 from the TOT group, 12 from the TVT group). Among respondents, no patients refused to be contacted at 5 years. We believe that the non-responding patients may have moved away and are in the process of re-tracing them. If we assume that all the women who have not responded are either lost to the study because they have moved away, or else will refuse to join when we do find them, we shall expect to include 86% of patients. If we assume a further 6% drop-out because they have moved away, died, or are unable to take part, that would leave 80% to take part in the study.

The experienced research nurse who is undertaking the study is already known to all study patients, and has established a good rapport with them. Follow-up at 5 years will be carried out at the Calgary Pelvic Floor Disorders Clinic. We believe that these factors will prove important in achieving good follow-up, by reducing the uncertainty involved in joining the follow-up study [15].

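### At 5 years the research nurse's assessments stay unblinded; this leaves the pad test and the recall questions, which she very probably runs, open to observer bias that could cheaply be reduced

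*Protocol article*

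**What the plan says.** All of this is in the Protocol article.

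- *Methods for protecting against sources of bias*, on the initial trial: "Outcome measurement was not carried out blindly, but was conducted by a research nurse who was independent of clinical care".
- The same section, on the new study: "In the 5 year follow-up, similar considerations will apply". The nurse who made the 12-month contacts "will contact and follow all women at 5 years". The safeguard restated for her is independence from clinical care.
- The same section then makes one change: "all clinical examinations will be carried out by a urogynaecology clinical fellow who will be blinded to both group of allocation", and also to the 12-month palpability finding.
- *Primary outcome: incidence of vaginal erosion or other serious adverse outcome* adds an outside adjudication committee: "They will be provided with all clinical details of the adverse outcome, with the cases blinded to group of allocation". Women are also asked there to recall problems they attribute to surgery. The text does not say who asks.
- *Objective outcome of SUI surgery at 5 years*: the pad test includes "coughing vigorously, 10 times; running on the spot for 1 min", and cure is a gain of under 1 g. Neither an operator nor blinding is stated.
- *Recruitment rate*: women are first contacted by "the research nurse who did all the patient contact and follow-up evaluations at 12 months". The reasons given for keeping her are rapport and retention.

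**The concern.** Being independent of clinical care is not the same as being blind to the arm. It removes a stake in the result of one's own surgery. It does not stop an expectation about the two procedures from affecting how hard a woman is urged to cough or run, or how far a vague complaint is followed up.

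Pad weight is objective, but the provocation that produces it depends on effort, and the result is cut at 1 g. A small difference in encouragement can therefore reclassify a woman who leaks little. With recall questions the risk is unequal probing, so that a problem is recorded in one arm and missed in the other.

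The authors treat knowledge of the arm as a threat: at 12 months examiner blinding could not be maintained, and they now use a blinded fellow. The other assessor is left as before. No section gives a reason why she needs to know the allocation. Contacting, scheduling and testing can all be done without it.

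**Working it through.** The plan states no figure for this point, so the first step is a comparison of passages. A small illustration for the pad test follows.

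**Step 1. Which 5-year measurements are blinded?**

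| Measurement | Assessor at 5 years | Blinding stated |
|---|---|---|
| Digital vaginal examination (erosion, palpable tape) | Clinical fellow | Yes: arm and 12-month palpability |
| Adjudication of primary events | Three outside urogynaecologists | Yes: arm |
| Chart review | Not named | Not stated |
| Recall of problems since surgery | Not named; very probably the nurse | No |
| Pad test | Not named; very probably the nurse | No |
| Subjective-cure item, UDI-6, IIQ-7, 15D | Apparently completed by the woman | No |

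That the nurse runs the pad test and asks the recall questions is an inference. It rests on three statements: she did all follow-up evaluations at 12 months, she follows all women at 5 years, and only clinical examinations pass to the fellow.

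**Step 2. Where could her knowledge of the arm enter?**

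- *Pad test.* Bladder volume, duration, repetitions and weighing are fixed. Vigour and encouragement are not. No later blinded step corrects the result.
- *Primary outcome.* Erosion comes from charts and the blinded examination. Other serious outcomes also draw on hospital charts and treating physicians, and the committee must agree before an event counts. The committee can reject an event put before it, but it cannot recover one that was never elicited. What remains exposed is a problem that is in no chart and is reported only if the woman is asked well.
- *Questionnaires.* If self-completed, they leave little room for an interviewer.

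**Step 3. Illustration for the pad test only.**

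Inputs from the documents:
- Expected group sizes (*Sample size and justification*): 0.8 × 94 = 75.2 and 0.8 × 105 = 84.0, which reproduces the stated 75 and 84.
- 12-month cure (*Background*): 68 women (81%) and 67 (77%). Denominators are 68/0.81 ≈ 84 and 67/0.77 ≈ 87, so pooled cure is 135/171 ≈ 79%.

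Assumptions not in the documents: true cure is 79% in both arms, and assessor behaviour shifts measured cure in one arm by 3, 5 or 10 percentage points.

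SE = √[0.79 × 0.21 × (1/75 + 1/84)] = 0.0647.

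Rejection probability of the nominal 5% test = P(|Z + shift/SE| > 1.96).

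| Assumed shift | Shift/SE | Normal approximation | Exact enumeration, uncorrected chi-square (range over arm and direction) |
|---|---|---|---|
| 3 points | 0.46 | 7.5% | 7.1–7.7% |
| 5 points | 0.77 | 12.1% | 11.1–13.1% |
| 10 points | 1.55 | 33.9% | 29.5–41.8% |

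The approximation serves for 3 and 5 points. At 10 points the answer depends on the direction: about 30% if measured cure is pushed down, 40–42% if it is pushed up.

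**The case against.** The strongest reply is that the limitation is disclosed and largely handled. The article says openly that measurement was not blinded. It repairs the examination where blinding had failed and adds an outside blinded committee. The pad test is standardised, the questionnaires look self-completed, and the pad-test operator is not named. The nurse did every 12-month evaluation, so masked forms cannot remove what she remembers. Her rapport is a stated reason for keeping her. Form layout and order of work are details an article commonly leaves to the full protocol.

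Much of this stands, and it narrows the point to the pad test and the recall questions. It does not remove it. The carry-over of unblinded measurement is a choice stated in the article's own bias section, not an omitted detail. Rapport is a reason to keep the nurse, not a reason for her to know the arm. Fixed repetitions do not fix effort.

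A reader might infer that the primary safety comparison is seriously exposed and attach a false-positive rate to it. The documents do not support that: a net shift would have to survive chart review, blinded examination and blinded adjudication. A reader might also take the team's published conclusion that TVT should remain the procedure of choice as evidence that the nurse is biased. It is the team's clinical conclusion and says nothing about her conduct.

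**Conclusion.** The point holds in a limited form. The plan carries unblinded assessment by the research nurse into the 5-year visit and states no blinding for the pad test or the recall questions. The main exposure is the secondary objective-cure outcome. For the primary outcome it is confined to uncharted events or persistent symptoms that are never elicited.

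The size is unknown. The rates of about 7%, 12% and 30–42% show only what assumed shifts of 3, 5 and 10 points would do to the pad-test comparison. They are not estimates of bias in this trial. The conclusion also rests on the inference that the nurse administers both assessments. If someone else does, the article should name that role and say whether the person is blinded. The change is worth making because it is cheap, but the weakness does not invalidate the design.

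**What to change.** In *Methods for protecting against sources of bias*, for the 5-year follow-up:

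1. State which role runs the pad test and asks the recall questions.
2. State that allocation and 12-month palpability are withheld from that person's contact list and visit forms.
3. State that both assessments use standard wording, including the encouragement given during the pad test, and are completed before any chart or operative note is opened.
4. Have the assessor record at the end of the visit whether the arm was known or guessed, and report this alongside the results.

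The cost is revised forms, a short script and a fixed order of work. Staffing, visits, sample size and significance level do not change, and the nurse keeps her contact role. Protection is partial: she may remember some allocations from 12 months and some women will disclose theirs. Item 4 lets readers judge what remains. A different, blinded person for the pad test would protect more but would need staff time; the point does not depend on it.
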